## Methods/Design

### Design

Randomised, double-blind, placebo-controlled experimental trial to determine the efficacy of plant sterol esters as dietary supplement in reducing lipids.

### Study setting and subjects

Patients diagnosed with hypercholesterolaemia will be recruited from 9 family doctors' surgeries at 3 healthcare centres in the health care area of Albacete, Spain.

The inclusion criteria are: a) subjects diagnosed with limit hypercholesterolaemia (total cholesterol 200-249 mg/dl) or defined hypercholesterolaemia (total cholesterol equal to or above 250 mg/dl) who have LDL-cholesterol levels equal to or above 130 mg/dl, b) subjects aged 18 years or over attending the participating health centres, c) subjects who give their consent to participate after being informed of the study objectives. The exclusion criteria are: a) known hypersensitivity to sterol esters or to the other components of the food that contains them (liquid yoghurt), b) contraindication for treatment with sterol esters or any of the components of the food, c) physical disability that hinders collaboration, d) significant chronic organic or psychiatric disease, e) not obtaining informed consent.

### Sample size

To obtain a 90% statistical power with an alpha error of 0.05 (bilateral hypothesis). The effect to be demonstrated is based on the following:

- The expected mean value of LDL-cholesterol in the patients included in the study is 157 mg/dl ± 30 SD (value obtained in previous studies conducted in a Spanish population).

- To demonstrate an effect of a 10% reduction in LDL-cholesterol in patients who receive the supplements, 152 subjects are needed (76 in the active group and 76 in the placebo group).

Assuming a 20% loss to follow up, 182 subjects will need to be selected and will be distributed equally between the two groups in order to obtain the maximum statistical power.

The recruitment period will be from January 2010 to September 2010.

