### Follow-up

The subjects will be followed-up for two years.

- Selection: patients who meet the inclusion criteria will be asked to participate in the study. After giving their informed consent they will be given an appointment for the initial visit and for the analytical tests.

- Initial visit: the participant will be randomised to one of the two groups. Their medical history will be taken and they will be given a physical examination. The corresponding dairy product will be dispensed (the following doses will be dispensed according to their expiry date). At this visit a lipid-lowering diet will be recommended to all the participants.

- Follow-up visits: at 1, 3, 6, 12, 18, and 24 months, the physical examination and analytical test parameters will be recorded. The cardiovascular risk will be calculated and possible adverse effects and compliance or adherence to the food supplied will be recorded.

The study will be finalised for the patient in the following circumstances: completed follow-up period (2 years), death, violation of the protocol, adverse event, intercurrent disease that makes it impossible to ingest food and patient abandons study or withdraws consent.

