### Primary variables and measuring methods

#### Primary variable

-Change in lipid profile at 1, 3, 6, 12, 18 and 24 months. Lipid levels will be measured in both plasma and capillary blood at the initial visit. The validity of the capillary blood lipid levels can be checked with the Cardiochek analyser (by total cholesterol, HDL-cholesterol and triglyceride strips, and subsequent calculation of LDL-cholesterol using the Friedewald formula). The measurements at 3, 12 and 24 months will be in plasma. At 1, 6 and 18 months they will only be in capillary blood.

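### The sample size uses the SD of LDL levels while the primary variable is change; plan on follow-up LDL adjusted for the initial value and restate the power for that analysis

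*Protocol article*

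**What the plan says.** The Sample size section of the protocol article sets its target as "To obtain a 90% statistical power with an alpha error of 0.05 (bilateral hypothesis"). Its only mean and SD are these: "The expected mean value of LDL-cholesterol in the patients included in the study is 157 mg/dl ± 30 SD". The effect and the resulting number follow: "To demonstrate an effect of a 10% reduction in LDL-cholesterol in patients who receive the supplements, 152 subjects are needed", split equally between the arms, and then "Assuming a 20% loss to follow up, 182 subjects will need to be selected".

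The Primary variable section declares "Change in lipid profile at 1, 3, 6, 12, 18 and 24 months". It also says that lipids are measured in both plasma and capillary blood at the initial visit, in plasma at 3, 12 and 24 months, and in capillary blood only at 1, 6 and 18 months.

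The section on the test of the hypothesis states the null hypothesis in terms of a decrease in LDL. The Efficacy analysis section compares means of the endpoint variables between groups at each follow-up by t test or Mann-Whitney test. It adds a repeated-measures model for total and LDL cholesterol levels, adjusted for changes in adherence. Baseline LDL is not named as a covariate.

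**The concern.** The variance that drives a sample size should be that of the quantity compared. Here the SD of 30 describes how much LDL levels differ between patients, whereas the declared outcome is how much each patient's LDL changes. The SD of a change depends on how strongly the initial and later values are correlated, and it can be larger or smaller than the SD of the levels. The article gives neither an SD of change nor a correlation, and it does not say that 30 is a deliberately cautious stand-in.

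Two things are at stake. First, the one stated power figure does not describe the declared outcome unless a particular correlation holds. Second, the choice of analysis matters. A comparison of raw changes is less precise than a comparison that ignores the initial value if the correlation is below 0.5. An analysis adjusted for the initial value is no less precise than either, under equal SDs. The initial plasma LDL is already collected, so the better analysis is available at no cost.

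**Working it through.** **Inputs from the Sample size section.** Two-sided alpha 0.05, power 90%, mean LDL 157 mg/dl, SD 30 mg/dl, 10% reduction, 76 per arm, 182 selected, 20% loss. The difference is 0.10 × 157 = 15.7 mg/dl.

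**Step 1: reproduce the stated number.** For two means,

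n per arm = 2 × (1.960 + 1.282)² × 30² / 15.7² = 76.7.

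The plan says 76, which agrees within rounding. At 76 per arm the power is 89.7% by the normal approximation and 89.3% by the noncentral t. Other settings do not give 76: one-sided 90% needs 63 per arm, two-sided 80% needs 58, and one-sided 80% needs 46. The calculation is therefore a two-group comparison with SD 30.

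**Step 2: the same design on raw change.** Assume that the SD is 30 at both times and let r be the correlation between them. Then

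SD of change = 30 × √(2(1 − r)).

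This equals 30 when 2(1 − r) = 1, that is, at r = 0.5. Randomisation makes the expected between-arm difference the same for change as for level, so 15.7 is kept. The documents give no r; 0.3 to 0.7 is an assumed range. Power below is two-sided, by the noncentral t.

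| Assumed r | SD of change | Power at 76 per arm | n per arm for 90% |
|---|---|---|---|
| 0.3 | 35.5 | 77% | 109 |
| 0.5 | 30.0 | 89% | 78 |
| 0.7 | 23.2 | 98.5% | 48 |

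**Step 3: adjust follow-up LDL for the initial value.** Under the same equal-SD assumption,

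residual SD = 30 × √(1 − r²).

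Since 1 − r² = (1 − r)(1 + r), it exceeds neither 1 nor, for r up to 1, 2(1 − r). The adjusted analysis is thus at least as precise as a comparison of levels or of raw changes.

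For a like-for-like comparison, take the number left after the planned loss: 182 × 0.8 = 145.6, or about 73 per arm.

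| Assumed r | Power, levels unadjusted (SD 30) | Power, raw change | Residual SD | Power, adjusted |
|---|---|---|---|---|
| 0.3 | 88% | 76% | 28.6 | 91% |
| 0.5 | 88% | 88% | 26.0 | 95% |
| 0.7 | 88% | 98% | 21.4 | 99% |

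**The case against.** The strongest reply is that nothing has been miscalculated. The stated number reproduces, and the treatment effect being powered, a between-arm difference of 15.7 mg/dl, is the same whether LDL is expressed as a level or as a change. The Efficacy analysis section does not tie the t test to change scores, and its repeated-measures model is worded in terms of levels. For a comparison of follow-up levels, an SD of levels is the right kind of SD. Using it when r is unknown is common, and it is conservative for change whenever r exceeds 0.5. A journal article may also leave the correlation to the full protocol.

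Most of this stands. It rules out calling the point an arithmetic error, and the absence of a printed r would not by itself be a finding. What remains is that the article prints its calculation and its declared outcome, and the two refer to different quantities with no stated link. It also plans no analysis that uses the initial LDL as a covariate.

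A reader might infer that the trial is underpowered. The documents do not support that: power on raw change at 76 per arm falls below 80% only if r is under about 0.35, and no r is given.

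A reader might also infer that 15.7 mg/dl is too large, because of the statement "At this visit a lipid-lowering diet will be recommended to all the participants" and because the Discussion mentions regression towards the mean, so that 10% would apply to a lower LDL. That does not follow either. The Discussion names regression to the mean only as a possibility, and the documents give no figure for a fall in the placebo arm. Any loss of power would further require the SD to stay at 30 as the mean falls. The Background also cites reductions of 15 to 20 mg at doses up to 2 g a day, a range that contains 15.7.

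**Conclusion.** The mismatch is real but limited. The 90% is the power of a two-group comparison of LDL levels with SD 30. It applies to the declared change only at r of about 0.5; over an assumed r of 0.3 to 0.7 the power on change runs from about 77% to 98.5% at 76 per arm. The error could lie in either direction, and the documents do not settle which.

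The conclusion rests on equal SDs at both times, on a difference of 15.7 mg/dl, and on reading the declared change in lipid profile as change in LDL. That last reading is supported by the general objective, the null hypothesis and the Sample size section, all of which name LDL.

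The point deserves action because a better analysis is at hand. At about 73 per arm, adjusting for the initial value raises power from about 88% to between 91% and 99% over the assumed range, and it removes the dependence on r being near 0.5.

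**What to change.** In the Efficacy analysis section, make the between-arm comparison of plasma LDL at follow-up, adjusted for initial plasma LDL, the planned efficacy analysis. This can be an ANCOVA, or the repeated-measures model already planned with baseline LDL added as a covariate.

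In the Sample size section, restate the power for that analysis with residual SD 30 × √(1 − r²). Give the assumed r and say that equal SDs are assumed. State 15.7 mg/dl as the between-arm difference at follow-up.

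The cost is a reworded paragraph in each of the two sections and a short recalculation. The initial plasma LDL and the plasma measurements at 3, 12 and 24 months are already in the schedule, so no patients, visits or samples are added. The stated power will then depend openly on an assumed correlation.

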#### Efficacy analysis

After the prior stages of data purification, exploratory analysis and categorisation or transformation of variables, the following were performed:

-Comparison of the variables of interest and the stratification and potentially confounding variables in both groups at the start of the study. Although we used a random assignment system, we checked that the baseline values of the study variables were uniform over the two groups.

-Classification of the subjects of the two groups into different LDL-cholesterol and total cholesterol reduction levels. A baseline raw analysis will be performed to evaluate the following parameters and their 95% confidence intervals: ABI (absolute benefit increase), RBI (relative benefit increase) and NNT (number needed to treat). A stratified analysis will be performed adjusted for each independent variable.

-The incidence of the endpoint variables in the two groups will be described and compared at each follow-up period (comparison of means using Student's t tests or Mann-Witney U test, depending on the distribution of the variables). The Friedman test will be used to compare the changes in lipid profile throughout the study in each of the groups.

-The effect of the dairy product on total cholesterol and LDL-cholesterol levels will be determined, adjusted for changes in adherence to the prescribed regimen (linear models generalised for repeated means).

-The convergent validity of the capillary blood measurements compared to the plasma measurements will be analysed through intraclass correlation.

The analysis will be an intention to treat analysis including all randomised patients in the efficacy analysis, according to their group and regardless of the treatment received. A per-protocol analysis will also be performed for the primary variables. Intermediate analyses will be performed to decide if the study should be prematurely terminated in the event of frequent adverse effects or a clear improvement in the test group (see Figure 1 for the study flow chart).

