## Discussion

The results of this study will provide valuable information on the efficacy of plant sterol ester supplements in preventing cardiovascular disease by lowering plasma cholesterol levels and consequently cardiovascular risk. If this supplement were effective a sounder recommendation for the consumption of plant sterols in subjects with hypercholesterolaemia could be made.

Possible limitations of the study - using a randomisation procedure reduces the risk of selection bias as the investigator will not assign treatment and any factor that effects participation will be balanced in the two groups. Confounding will also be reduced as randomisation tends to divide the determinant factors, which influence the final result, equally between the two groups. However, bias could exist on collecting information due to the regression towards the mean effect or tendency of the continuous variables towards the mean in successive measurements, applicable to the analytical results. There is also a possible risk of differential loss to follow up between the two groups, due to the length of the study and also to the placebo effect which could contribute to the patients abandoning the study because they consider that the treatment provided is not having any effect.

The study protocol has been evaluated and approved by the Institutional Review Board of the Albacete Health Area on 23rd April, 2009. During the performance of the study the following ethical principles will be respected: voluntary participation with consent of the patient, guarantee of anonymity in the information provided by the patient, data provided by the patient exclusively restricted to use in the proposed study. The investigators will ensure that the study is conducted in accordance with the declaration of Helsinki and with legislation in effect (Royal Decree 223/2004) and the New Code of Medical Ethics of the Spanish Medical Association. The study will fully comply with Good Clinical Practice principles.

Finally, for the development of this project the following principles have been considered: 1) data on the dairy product are sufficient to guarantee that the risk to the study participants is acceptable; 2) the objectives of the study will probably provide further knowledge of the topic to be studied; 3) the available information warrants the performance of this study and its potential risk to the participants.

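### The 90% power describes 152 analysed patients with the full 10% LDL effect, not the intention-to-treat analysis of all 182 randomised, for which no dilution is allowed

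*Protocol article*

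**What the plan says.** Under Sample size, the protocol asks for 90% power at a two-sided alpha of 0.05. Its planning value is: "The expected mean value of LDL-cholesterol in the patients included in the study is 157 mg/dl ± 30 SD". The target is set for those who take the product: "To demonstrate an effect of a 10% reduction in LDL-cholesterol in patients who receive the supplements, 152 subjects are needed". That makes 76 per arm. Loss is then handled by adding patients: "Assuming a 20% loss to follow up, 182 subjects will need to be selected and will be distributed equally between the two groups".

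Under Efficacy analysis, the population is fixed: "The analysis will be an intention to treat analysis including all randomised patients in the efficacy analysis, according to their group and regardless of the". The sentence ends by setting aside what patients actually took. The primary variables are to be analysed per protocol as well.

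Under Follow-up, the study ends early for a patient who, among other reasons, abandons it, withdraws consent, violates the protocol or has an adverse event. The Discussion expects some of this. It names the length of the study and the possibility of "patients abandoning the study because they consider that the treatment provided is not having any effect".

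**The concern.** The sample size uses the full effect and treats the 20% loss purely as missing heads. The intention-to-treat rule does not remove those heads. It keeps every randomised patient in the assigned group.

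A patient who has left no longer receives the yoghurt. The Background describes the action as inhibition of intestinal cholesterol absorption, so an effect that fades off product is a reasonable inference, although the protocol does not state it. If such patients contribute 24-month values, the expected difference between groups is smaller than 15.7 mg/dl. If they do not, fewer than 152 patients are analysed. In neither case does the 90% follow from the stated inputs. At stake is how a reader judges a non-significant main result: the chance of missing a true effect could be up to about twice the stated 10%.

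**Working it through.** **Inputs (Sample size section).** Mean LDL-cholesterol 157 mg/dl, SD 30, two-sided alpha 0.05, power 90%, equal allocation, 20% loss, 182 randomised (91 per arm). The difference is 0.10 × 157 = 15.7 mg/dl. The effect kept by lost patients is not given, so it is varied from 0% to 100%.

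**Reproducing the stated size.** Patients per arm = 2 × (1.960 + 1.282)² × 30² / 15.7² = 76.7, against the stated 76. Power with 76 per arm from the noncentral t distribution is 89.3% (normal approximation 89.7%). The stated 152 is thus reproduced within rounding, on the full 15.7 mg/dl.

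**Loss as a head count.** 152 × 1.2 = 182.4, which matches 182. A 20% loss from 182 leaves 182 × 0.8 = 145.6, about 146 patients (73 per arm). With the full effect in all of them, power is 88.1%.

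**Intention to treat on all 182.** If a fraction k of the effect is kept by the lost 20%, the expected difference is 15.7 × (0.8 + 0.2k). Noncentral-t power with 91 per arm and SD 30:

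| Effect kept by lost patients (k) | Difference, mg/dl | Power |
|---|---|---|
| 0% | 12.56 | 80.2% |
| 25% | 13.35 | 84.7% |
| 50% | 14.13 | 88.5% |
| 75% | 14.92 | 91.6% |
| 100% | 15.70 | 94.0% |

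Allowing for the extra spread of a mixed active arm changes the first row little. The active-arm variance becomes 900 + 0.2 × 0.8 × 15.7² = 939.4, the SD averaged over both arms is 30.33, and power is 79.4%.

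**Break-even.** 90% power with 91 per arm needs a difference of about 14.5 mg/dl. Solving 15.7 × (0.8 + 0.2k) = 14.5 gives k of about 0.62.

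**Chance of conflicting results.** In 20,000 simulated trials, 73 of 91 active patients were shifted by 15.7 mg/dl and the other 18 by nothing, and the per-protocol set was 73 against 73. A significant per-protocol result with a non-significant intention-to-treat result occurred in about 10% of trials.

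**The case against.** The strongest reply is that the protocol's 20% is loss to follow-up, not stopped treatment with LDL still measured. A lost patient has no 24-month value, so the diluted 12.56 mg/dl arises only if that value is supplied in some way that carries no product effect. The protocol does not say this will be done, and handling of missing values may be set in an analysis plan that is not shown. This stands. A reader might infer that intention-to-treat power simply is 80%, but the documents do not support that. It is the result under one assumption, at the low end of an 80% to 94% range.

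Second, the phrase about recipients may mean no more than the active arm, and the 10% drawn from earlier trials may already average over imperfect adherence. That is possible and cannot be checked here. It would soften the dilution, but it does not restore 90% if the lost patients are left out: that figure is still 88%.

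Third, the 20% is presumably cumulative over 24 months, so any dilution would be smaller at the earlier visits. The SD of 30 also describes LDL level, whereas the primary variable is a change. With full dilution and an assumed baseline correlation of 0.3 to 0.7, normal-approximation power runs from about 67% to 95% for change scores, using SD 30 × √(2(1 − r)). With baseline adjustment, using SD 30 × √(1 − r²), it runs from about 84% to 98%. The protocol gives no correlation. The figures above therefore hold on its own planning basis only.

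A reader might also infer that a positive per-protocol result beside a negative intention-to-treat result is likely. At about 10% even under full dilution, it is not.

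**Conclusion.** The point holds in a conditional form. The 90% belongs to 152 analysed patients showing the full 15.7 mg/dl difference. The protocol names a different analysis, of all 182 randomised, and makes no allowance for dilution. On its own SD, alpha and loss rate, 24-month power is about 80% to 89% if lost patients are analysed and keep none to half of the effect, and about 88% if they are not analysed. It reaches 90% only if they are analysed and keep about 62% or more.

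It would be wrong to conclude that the 90% can be reassigned to completers, because 182 randomised leave about 146 of them, not 152. Raising the total to 152 / 0.8 = 190 would correct that head count, but under full dilution it gives only 81.9%. The inflation step and the dilution are separate matters.

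**What to change.** Keep 182 patients and reword the Sample size section. For example: the 90% refers to 152 subjects analysed with the full 10% effect; with 182 randomised and 20% lost, power at 24 months is about 88% for about 146 completers, and about 80% to 89% for intention to treat on all randomised if lost patients keep none to half of the effect. State that the share of effect kept is an assumption.

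The cost is a change of wording, with no extra patients or procedures. The downside is a less favourable stated power for the main analysis.

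### The 20% loss allowance is added to 152 rather than divided out, so 182 patients cover a loss of only 16.5% and give about 88% power, not 90%, at the assumed loss

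*Protocol article*

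**What the plan says.** All the figures are in the Sample size section of the protocol article.

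- The target is set by "To obtain a 90% statistical power" with an "alpha error of 0.05 (bilateral hypothesis").
- LDL-cholesterol is expected to average 157 mg/dl with an SD of 30. The effect is given as "To demonstrate an effect of a 10% reduction in LDL-cholesterol in patients who receive the supplements".
- On that basis "152 subjects are needed (76 in the active group and 76 in the placebo group").
- The allowance for losses follows: "Assuming a 20% loss to follow up, 182 subjects will need to be selected". The same sentence adds that these patients "will be distributed equally between the two groups".

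No other loss rate or inflation rule is given. The Efficacy analysis section names a "comparison of means using Student's t tests or Mann-Witney U test" for each follow-up period. The Follow-up section sets the duration: "The subjects will be followed-up for two years".

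**The concern.** Three of the stated figures cannot all be true: 152 evaluable patients needed, 20% lost, 182 enrolled. Taking 20% away from 182 leaves fewer than 152. The 182 appears to come from adding 20% to the evaluable number, which treats the loss as a fraction of those who remain rather than of those who enter.

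The allowance exists to protect the stated power against losses over two years, and the Discussion itself names differential loss as a risk because of the length of the study. As written, the allowance falls short at exactly the loss rate that the plan assumes. What is at stake is the accuracy of the stated power and loss tolerance. The design, the choice of test and the type I error are unaffected.

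**Working it through.** **Inputs** (all from Sample size): two-sided alpha 0.05, z = 1.960; power 90%, z = 1.2816; SD 30 mg/dl; difference 10% of 157 = 15.7 mg/dl; equal allocation. The comparison of two means comes from Efficacy analysis.

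**1. Reproduce the evaluable number.**

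n per arm = 2 × (1.960 + 1.2816)² × 30² / 15.7² = 76.7

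The stated 76 per arm (152 in total) agrees to within one patient per arm. Other settings do not fit: a one-sided test gives 63 per arm, and 80% power gives 58. The base figure is therefore understood and taken as it stands.

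**2. Reproduce the inflated number.**

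- Multiplying: 152 × (1 + 0.20) = 182.4, stated as 182.
- Dividing: 152 / (1 − 0.20) = 190.

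Multiplication reproduces the plan's figure. Division, which is what keeps 152 after the loss, differs by 190 − 182 = 8 patients (8/182 = 4.4%), too much for rounding.

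**3. What 182 delivers.**

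- Remaining after 20% loss: 182 × 0.80 = 145.6, or 72.8 per arm (about 73), against 152 required.
- Loss that still leaves 152: 1 − 152/182 = 16.5%.
- Check on the alternative: 190 × 0.80 = 152 exactly.

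**4. Power.** With the normal approximation, power = Φ(15.7 / (30 × √(2/n)) − 1.960).

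- n = 73: 15.7 / 4.966 = 3.162; Φ(1.202) = 88.5%
- n = 76: 15.7 / 4.867 = 3.226; Φ(1.266) = 89.7%

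| Evaluable per arm | Situation | Normal | t test |
|---|---|---|---|
| 73 | 182 allocated, 20% lost | 88.5% | 88.1% |
| 76 | the plan's evaluable number | 89.7% | 89.3% |
| 91 | 182 allocated, none lost | 94.2% | 94.0% |

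The loss step costs 89.7 − 88.5 = 1.2 points (normal) or 89.3 − 88.1 = 1.2 points (t test). The rest of the distance to 90% comes from rounding 76.7 down to 76.

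**The case against.** **The 182 might be a number to screen.** The verb used would allow that reading, but the same sentence divides these patients between the two groups. They are the allocated patients, so this does not rescue the figure.

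**The effect is small.** This stands. Eight patients and about 1.2 points of power would not change how the trial is run.

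**The 88% is conditional.** This also stands. It assumes that only completers contribute, that the full 20% is lost at the visit in question, and that the SD is 30 without adjustment. The Efficacy analysis section plans an intention-to-treat analysis of everyone randomised, comparisons at each visit and models for repeated measurements. If 20% is the cumulative two-year loss (the document does not say when losses occur), earlier visits keep more patients; with no loss, 91 per arm gives about 94%. The 88% is thus a late-visit, completer-only figure. None of this alters the arithmetic: the Sample size section itself treats lost patients as unusable, and its three numbers still conflict.

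**Stronger readings that the document does not support.**

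- A reader might infer that the 152 is wrong too, because 76.7 would normally be rounded up and an exact t-test formula gives slightly more. The section names no formula, and the difference is a matter of rounding.
- A reader might infer that the loss step raises the type II error from 10% to 12%. That comparison mixes the loss step with the rounding of 76.7; 76 per arm already falls slightly short of 90%.
- A reader might infer that the trial is materially underpowered, or that a null result would be misjudged. A null result would be interpreted mainly from its confidence interval, and 88% against 90% would hardly change that reading.
- A reader might infer that baseline adjustment certainly makes good the shortfall. It may, but that depends on a baseline-to-follow-up correlation that the document does not state.

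**Conclusion.** The sentence is wrong as written, with minor to moderate severity. The 182 was obtained by multiplying 152 by 1.2 and is 8 short of the 190 that keeps 152 after 20% loss. It covers a loss of 16.5%.

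At the assumed 20%, about 73 per arm remain and power is about 88% instead of the stated 90%. The arithmetic on numbers of patients needs no assumption beyond the plan's own figures. The power figure rests on a 15.7 mg/dl difference, SD 30, two-sided 0.05, completers only and no adjustment. The case for correcting it is that a stated figure is inaccurate and cheap to put right, not that the trial is seriously harmed.

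**What to change.** Restate the one sentence in the Sample size section in either of these ways:

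- 182 randomised patients allow for a loss of 16.5% while keeping 152 evaluable; or
- 182 randomised patients with 20% loss leave about 73 per arm and give about 88% power (15.7 mg/dl, SD 30, completers, unadjusted).

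If both the 90% power and the 20% loss are to be kept, the total consistent with 152 evaluable is 190, which is 8 more than stated.

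The text may add that baseline adjustment could recover the small shortfall, provided it says that this depends on a correlation not yet given.

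The first two options cost a sentence and a slightly less favourable power or loss statement, and remain open even if recruitment has finished. The third costs 8 more patients. None changes a procedure or the analysis.
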